### Sample size estimation

2.4

According to a previous study a sensitivity and specificity for AFib detection per patient of >99 and 90%, can be assumed, respectively (18). Thus, 40 cases of AFib are required to estimate the sensitivity with a precision of about 10%, i.e., the difference of the lower bound of a two-sided exact 95% confidence interval and the point estimate of the sensitivity is 10%. As other studies observe paroxysmal AFib in 9%−16% of patients with cryptogenic stroke (4, 5), we intend to enroll 400 patients to obtain the required 40 cases. The specificity can consequently be measured with a precision of 4%. Our inclusion criteria should lead to a preselection of candidates with increased AFib risk factors. Therefore, AFib detection rate might increase up to 28% (max = 112) in our cohort within 6 months (8). The event of a 10% drop-out rate (e.g., due to withdrawal of consent, eligibility violations, no intervention, or non-existent data after inclusion into the study) would result in a minimum of 36 AFib cases and a similar precision of estimation i.e., 12% for the sensitivity and 4% for the specificity.

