### Statistical methods and analysis populations

2.5

Point estimates and two-sided exact 95% confidence intervals will be computed for the sensitivity and specificity referring to the primary objectives, related secondary objectives and subgroup analyses. Cardiologist-supervised event recorder-based continuous ECG rhythm analysis serves as the gold standard. Thus, in the case of discordant results, we consider the analysis of the signal from the event recorder by the cardiologist as the true status. As power calculation is based on participants with detected AFib as effective sample size (n_AFib_), we intend on analyzing our data as soon as one of the following situations occurs: (1) AFib is detected in 40 participants, who have completed follow-up or (2) enrolment and follow up is complete for all 400 participants (n_Enrolment_). In the first situation, the study leadership, the statistician, and the steering committee will decide on continuation of enrolment. Exploratory hypothesis testing of comparisons will be performed by McNemar's Chi-squared Test at two-sided 5% levels of significance. Due to the exploratory character of the analysis, and in accordance with the calculation of 95% confidence intervals, there will be no correction for multiple testing. With reference to the ICH E9 Guideline, the analyses will be performed using a full analysis set (FAS), according to the intention-to-treat principle (ITT), and a per protocol set (PP). The former will include all times with event recorder measurements (until possible but unexpected losses to follow-up) and the latter will include only times with additional smartwatch recordings. Therefore, missing values, possibly due to non-compliance, will be rated as no signal of an AFib by the smartwatch in the FAS. The FAS and PP analysis populations coincide when smartwatch records are available in all patients. Patients with eligibility violations (concerning inclusion or exclusion criteria), no intervention or non-existent data after inclusion into the study will be excluded from analysis. Time to confirmed AFib diagnosis, count of AFib diagnoses, AFib burden, safety endpoints and usability of smartwatches will be reported by descriptive statistics (mean, standard deviation, median, interquartile range, absolute and relative frequency). AFib risk factors will be compared between patient groups with and without AFib using descriptive statistics, hypothesis testing and multiple logistic regression models. Pre-defined subgroup analyses will be performed as described above.

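### The stated 4% specificity precision belongs to full enrolment and is not secured if enrolment stops at the 40-case trigger when the AFib rate is above about 14%

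*Protocol article*

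**What the plan says.** Section 2.2.1 (Primary objectives) makes per-patient sensitivity and specificity at 6 months the joint measure of accuracy.

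Section 2.4 (Sample size estimation) starts from "a sensitivity and specificity for AFib detection per patient of >99 and 90%, can be assumed, respectively". It says that "40 cases of AFib are required to estimate the sensitivity with a precision of about 10" per cent, and explains precision as "the difference of the lower bound of a two-sided exact 95% confidence interval and the point estimate of the sensitivity is 10" per cent. Taking AFib rates of 9% to 16% from other studies, it plans 400 patients to obtain the 40 cases, and then adds "The specificity can consequently be measured with a precision of 4" per cent. With 10% drop-out it expects at least 36 cases and still 4% for specificity. The same paragraph says that, because of the risk-factor inclusion criteria, "AFib detection rate might increase up to 28% (max = 112) in our cohort within 6 months".

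Section 2.5 (Statistical methods and analysis populations) treats participants with detected AFib as the effective sample size. The data are to be analysed at the first of two events: "AFib is detected in 40 participants, who have completed follow-up", or completion of enrolment and follow-up for all 400. If the first event occurs, "the study leadership, the statistician, and the steering committee will decide on continuation of enrolment". No minimum number of AFib-free patients is attached to the trigger or to that decision.

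**The concern.** Sensitivity is estimated in patients with AFib and specificity in patients without it. The 40-case trigger fixes the first denominator and leaves the second to the AFib rate. The higher the rate, the sooner 40 cases accrue and the fewer AFib-free patients have been followed by then.

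The inclusion criteria are meant to raise the AFib rate, and the Discussion presents this as a gain in study power. That is true for sensitivity. For specificity, if enrolment ends at the trigger, it works the other way. At stake is whether a precision stated for half of the primary objective describes the data set that may actually be analysed.

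**Working it through.** **Inputs**
- Specificity 90%; precision defined as point estimate minus lower confidence bound; 40 cases; 400 enrolled; AFib rate 9% to 16%, possibly up to 28%; 10% drop-out (all section 2.4).
- Two-sided exact 95% intervals: "Point estimates and two-sided exact 95% confidence intervals will be computed for the sensitivity and specificity" (section 2.5).
- Assumption: at the trigger, only patients with completed follow-up are analysed.

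**Formulas**
- Exact (Clopper-Pearson) lower bound for x AFib-free patients correctly classified out of n: the 2.5% quantile of a Beta(x, n − x + 1) distribution, with x = 0.9n.
- Precision = 0.90 − lower bound.
- Expected AFib-free patients when 40 cases are reached at AFib rate r: n = 40/r − 40.

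**Step 1: the protocol's own figures**
- Full enrolment: 400 − 40 = 360 AFib-free, lower bound 0.864, precision 3.6 points.
- After 10% drop-out: 360 − 36 = 324 AFib-free, lower bound 0.862, precision 3.8 points.
- Both round to the stated 4%. The sensitivity figures also reproduce: 39 of 40 gives 10.7 points, 99% of 40 gives 9.7, and 35 of 36 gives 11.8 (stated: about 10% and 12%).

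**Step 2: stopping at 40 cases**

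| AFib rate | Completed patients (40/r) | AFib-free | Precision, points |
|---|---|---|---|
| 10% | 400 | 360 | 3.6 |
| 12% | 333 | 293 | 4.0 |
| 14% | 286 | 246 | 4.45 |
| 16% | 250 | 210 | 4.9 |
| 20% | 200 | 160 | 5.7 |
| 28% | 143 | 103 | 7.5 |

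**Step 3: where the 4% gives way**

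The protocol rounds 3.6 and 3.8 to 4%, so the fair limit is 4.5 points. Staying below it needs 242 AFib-free patients, and 40/(40 + 242) = 14.2% AFib. Staying below an unrounded 4.0 points needs 297.

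**Step 4: is the trigger likely to be reached?**

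The binomial chance of at least 40 cases among 400 is 52% at 10% AFib, 91% at 12%, and over 99% at 14% and above. Where the precision matters, the trigger is almost certain to be met.

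**Step 5: continuing to the cap**

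At 28% AFib, the full 400 gives 400 × 0.72 = 288 AFib-free and 4.1 points. After 10% drop-out it is 360 × 0.72 = 259 and 4.3 points. Both round to 4%.

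**Sensitivity of the result**

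At 16% AFib the shortfall depends on the lower-bound definition: the half-width of the exact interval is 4.3 points and the Wald half-width 4.1. At 28% every definition exceeds 4% clearly (5.8 Wald, 6.3 half-width, 7.5 lower-bound distance). If true specificity were 95%, 210 AFib-free patients would give 3.9 points and 103 would give 6.2.

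**The case against.** The strongest reply is that section 2.4 states the 4% for 400 enrolled, where it is right, and that section 2.5 openly lets the number of AFib cases drive the timing. That stands: there is no arithmetic error, and letting sensitivity lead is a legitimate choice. What it leaves open is that the reader gets one precision figure and two possible analysis points, and the figure fits only one of them at higher AFib rates.

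The consequence is also limited. The study estimates accuracy with confidence intervals, sets no success threshold for specificity, and will report the interval achieved. Even 7.5 points is tighter than the 10 to 12 points accepted for sensitivity. This stands and lowers the severity.

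Three stronger readings are tempting, and the text does not support them.

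- A reader might infer that the trigger ends the trial. It does not: it leads to a decision on continuing enrolment, and continuing largely restores the 4%. Patients still in follow-up at the trigger could also add AFib-free patients if analysed later; accrual is not stated, so their number cannot be computed.
- A reader might infer that the committees decide with smartwatch accuracy in view, which would bias the estimates. Section 2.5 does not say so. The decision is tied to the first situation, which can mean simply that the count has been reached.
- A reader might infer that smartwatch detections count toward the 40. The trigger names no device, and the detection alert in section 2.1 is device-neutral. But section 2.5 makes the cardiologist-read recorder signal the true status, so recorder-confirmed cases are the natural reading. Naming the recorder is a clarification only.

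**Conclusion.** The point holds in a limited form. The 4% is correct at full enrolment. It is not secured if enrolment stops at 40 cases: the expected precision is about 4.5 points at 14% AFib, 4.9 at 16%, 5.7 at 20% and 7.5 at 28%. At 9% to about 14% AFib the stated figure stands on the protocol's own rounding. At 16%, the top of the range cited from other studies, the shortfall is modest. It is material only at the enriched rates, which the protocol presents as possible, with 28% as the maximum.

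These figures assume 90% specificity, expected counts at the trigger, analysis of completed patients only, and a decision to stop. That last decision is discretionary, and nothing stated ties it to specificity. The point should be fixed before the trigger is reached, but it does not undermine the design.

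**What to change.** In section 2.4, state the specificity precision as about 4% at full enrolment and up to about 7.5% if enrolment stops at the 40-case trigger, depending on the AFib rate.

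In section 2.5:
- Word the first trigger as 40 participants with event-recorder-confirmed AFib who have completed follow-up.
- Base the continuation decision on the recorder-positive and recorder-negative counts, before smartwatch accuracy is tabulated.
- If the sponsor wants to keep about 4%, continue toward the existing cap of 400 until roughly 240 to 300 recorder-negative patients have completed follow-up.

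A fixed minimum of 300 recorder-negative patients is not advisable. It cannot be reached within 400 above 25% AFib (300/400 = 75% AFib-free), or above about 17% after 10% drop-out (300/360 = 83%), and so would largely remove the early trigger. A floor near 240 remains within reach even at 28% AFib after drop-out (259 expected).

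The cost is a few sentences and no patients beyond the planned 400. The downside is a less favourable stated precision or, if the 4% is kept, a later analysis when the AFib rate is high. The delay is a real cost, because the Discussion already names recruitment as a challenge.

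### The decision at 40 AFib cases on whether to continue enrolment is not shielded from the accuracy results, so it can depend on them; the likely effect is modest and easily removed

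*Protocol article*

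**What the plan says.** Section 2.5 (Statistical methods and analysis populations) treats the number of AFib cases as the effective sample size and states that "we intend on analyzing our data as soon as one of the following situations occurs". The first situation is AFib in 40 participants with completed follow-up. The second is completion of enrolment and follow-up for all 400. The next sentence reads: "In the first situation, the study leadership, the statistician, and the steering committee will decide on continuation of enrolment".

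No criterion for that decision is given. Nothing says that the three parties decide without sight of the accuracy results, or which analysis is final if enrolment goes on. The reported quantities are fixed-sample ones: "Point estimates and two-sided exact 95% confidence intervals will be computed for the sensitivity and specificity". The only monitoring body described (section 2.3) has a quality-assurance remit and no stated part in this decision.

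**The concern.** An analysis followed by a decision on further enrolment is an interim look. If the look shows watch-versus-recorder accuracy, the final sample size can depend on the estimate itself. Stopping after a high estimate freezes a favourable chance deviation, while continuing after a low one dilutes an unfavourable one. Both accuracy measures would then be too high on average, and a fixed-sample exact interval no longer guarantees at most 2.5% error in each tail. The point estimates and intervals are the whole primary result of this study, so an error in them is an error in its main message.

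**Working it through.** **Inputs.** Section 2.4 gives the planning values: "a sensitivity and specificity for AFib detection per patient of >99 and 90%, can be assumed, respectively" (99% is used below for sensitivity). It also gives the size, "we intend to enroll 400 patients to obtain the required 40 cases", and the upper AFib rate, "AFib detection rate might increase up to 28% (max = 112) in our cohort within 6 months". The expected AFib range is 9% to 16%, and 16% of 400 is 64 cases. Assumed here, because the article gives no rule: stop at n1 if the number of correct results x1 is at least c, otherwise continue to n2, and report the ordinary Clopper-Pearson interval. Every threshold c was tried.

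**1. The plan's own precision reproduces.** With 40/40 detected the lower limit is 0.025^(1/40) = 0.912, a distance of 8.8 points. With 39/40 it is 97.5 − 86.8 = 10.7 points. The expected distance at a true 99% is 9.5, so about 10 is right. Specificity 324/360 gives 3.6 points, stated as 4.

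**2. The 40-case trigger is realistic.** The binomial chance of at least 40 cases among 400 is 27% at an AFib rate of 9%, 52% at 10%, 91% at 12% and over 99.9% at 16%. Expected enrolment to yield 40 cases is 40/0.16 = 250, or 40/0.28 ≈ 143.

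**3. Bias.** Let D = x1/n1 − p, and let S = 1 if the trial stops. The expected error of the final estimate is E[D·S] + (n1/n2)·E[D·(1−S)]. Since E[D] = 0, this equals (1 − n1/n2)·E[D·S]. For 40 to 112 the factor is 1 − 40/112 = 0.643. At p = 0.80 the worst threshold is c = 33, with E[D·S] = 0.025, so the bias is 0.643 × 0.025 = 0.016, or 1.6 points.

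**4. Lower-tail error.** Take p = 0.83 and c = 38. The lower limit for 38/40 is 0.8308, just above 0.83, so every early stop misses. P(x1 ≥ 38) = 780(0.83^38)(0.17²) + 40(0.83^39)(0.17) + 0.83^40 = 0.0190 + 0.0047 + 0.0006 = 0.0243. That alone nearly uses up the 2.5%. Misses after continuation to 112 bring the total to 4.2%.

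**5. Worst case over all thresholds.** Each maximum is taken separately. For specificity, n1 = 143 − 40 = 103 and n2 = 400 − 112 = 288 at 28% AFib; n1 = 250 − 40 = 210 and n2 = 400 − 64 = 336 at 16%. These expected counts are treated as fixed.

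| Measure | True value | n1 to n2 | Bias (points) | Lower-tail error | Total non-coverage |
|---|---|---|---|---|---|
| Sensitivity | 80% | 40 to 112 | 1.6 | 2.0% | 3.9% |
| Sensitivity | 83% | 40 to 112 | 1.5 | 4.2% | 6.3% |
| Sensitivity | 85% | 40 to 112 | 1.4 | 3.0% | 4.4% |
| Sensitivity | 90% | 40 to 112 | 1.2 | 2.3% | 3.8% |
| Sensitivity | 91% | 40 to 112 | 1.2 | 4.1% | 6.4% |
| Sensitivity | 99% (planned) | 40 to 112 | 0.4 | 0.0% | below 1% |
| Specificity | 85% | 103 to 288 | 0.9 | 3.9% | 6.3% |
| Specificity | 90% (planned) | 103 to 288 | 0.8 | 3.2% | 5.4% |
| Specificity | 90% (planned) | 210 to 336 | 0.3 | 3.0% | 4.8% |

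With n2 = 64, the sensitivity bias is 0.9 points at a true 80%, and the lower-tail error peaks at 3.4% near 82.5%. The worst bias and the worst tail error come from different thresholds: at 83%, c = 38 costs 4.2% in the tail but only 0.2 points of bias.

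**The case against.** A reader might infer that the deciders will have the results in hand, choose freely, and let a favourable interim result become the final one. The article does not establish that. The order of analysing first and deciding second is the natural reading of two adjacent sentences, but it is not spelled out. The trigger is a case count. If that count is recorder-confirmed, which fits the recorder's role as the true status, it does not depend on how the watch performs. No success threshold exists, hypothesis testing is called exploratory, and no motive can be read from the text. A full protocol, analysis plan or committee charter that is not shown may hold a rule.

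The numbers also need care. Every threshold above is assumed, and one decision cannot be worst-case for sensitivity and specificity at once. The largest specificity figures need 28% AFib, a specificity below plan and an unlucky threshold together. Patients still in follow-up when enrolment stops may add cases. If a stopped trial ends with m cases, the bias factor falls from 1 − 40/112 to 40/m − 40/112. With m = 56 as an illustration, that is 0.357 instead of 0.643, and 1.6 points becomes 0.9.

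These points stand and limit the size of the concern, but they do not remove it. The article itself sets an analysis at 40 cases and a discretionary decision tied to it, and nothing separates the two. Sensitivity below 99% is also plausible. The Discussion says that data from healthy people cannot simply be transferred to stroke patients, and section 2.5 counts missing watch data as no AFib signal in the full analysis set. The built-in conservatism of exact intervals often absorbs the effect, but not always, as the 83% and 91% rows show.

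**Conclusion.** The plan as written permits the decision on further enrolment to depend on observed accuracy, while the final intervals assume a fixed sample size. It does not show that the decision will be made that way. If good results stop enrolment, both measures are biased upward by a modest amount: for sensitivities of 80% or more, at most about 1.6 points, with lower-tail error up to about 4.2%. For specificity the figures are 0.9 points and 3.9% at a true 85%, and 0.8 points and 3.2% at the planned 90%. At the planned sensitivity the bias is at most 0.4 points and coverage holds.

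These are upper ends under assumed thresholds, with 112 cases available if enrolment continues and exactly 40 if it stops. They are small beside a precision of about 10 points for sensitivity, and they do not make the planned intervals useless. The point deserves correction because the error runs in one direction, towards better apparent accuracy, and the remedy is simple.

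**What to change.** Add to section 2.5 that the continuation decision at 40 cases uses only the count of recorder-confirmed AFib cases, enrolment and resources. State also that the aggregated watch-versus-recorder comparison is neither produced nor shown to the study leadership, the statistician or the steering committee until enrolment is closed and all enrolled patients have completed follow-up. The daily reading of individual signals by the core laboratory and the access of sites to their patients' data (section 2.1) continue as planned, so the restriction covers the aggregated comparison only.

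This needs about two sentences, no added patients and no change to the interval method. The freedom to stop or continue is kept. The cost is that the deciders give up seeing accuracy results before they decide.

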#### Primary objectives

2.2.1

The primary objective is to assess whether AFib detection via smartwatch in patients suffering from cryptogenic TIA/ischemic stroke is accurate in comparison to implantable event recorders. This will be assessed by sensitivity and specificity of AFib detection per patient after 6 months. We aim on a comparison of smartwatch based, continuous, automated, cardiologist supervised rhythm analysis of photoplethysmography (PPG)- signal and patient activated one-lead ECG with event recorder based, continuous, automated ECG rhythm analysis.

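### In the FAS, scoring missing smartwatch data as no AFib is conservative for per-patient sensitivity but flatters per-patient specificity

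*Protocol article*

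**What the plan says.** Section 2.2.1 (Primary objectives) makes the primary measure "sensitivity and specificity of AFib detection per patient after 6 months". The truth is set by the recorder: "Cardiologist-supervised event recorder-based continuous ECG rhythm analysis serves as the gold standard" (section 2.5).

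Section 2.5 plans two analysis sets. Of the FAS it says: "The former will include all times with event recorder measurements". Of the PP set it says that "the latter will include only times with additional smartwatch recordings". For the FAS it then fixes how gaps are handled: "missing values, possibly due to non-compliance, will be rated as no signal of an AFib by the smartwatch in the FAS". Patients with eligibility violations are left out, and so are those with "no intervention or non-existent data after inclusion into the study will be excluded from analysis". Neither set is named as primary. Exact intervals are planned for the primary measures, the related secondary measures and the subgroups.

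Section 2.2.3 (Secondary objectives) adds sensitivity and specificity by recorded or analysable time. Section 2.2.2 predefines subgroups with residual deficits or NIHSS ≥8, because use of the watch may be impaired there. The Discussion puts compliance problems or losses to follow-up at around 5% to 10%.

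**The concern.** One imputation rule serves two measures on which it acts in opposite directions. In a recorder-positive patient, a missing watch value becomes a missed case. In a recorder-negative patient, it becomes a correct result, although the watch may have had little chance to raise a false alarm.

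The FAS specificity thus mixes two things: how well the watch discriminates, and how little it was worn. At stake is the reading of one of the two primary measures. It matters most in the subgroups singled out for expected difficulty with the watch, where lower wear would appear as higher specificity.

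**Working it through.** **Inputs.** From section 2.4: assumed sensitivity >99% and specificity 90%, 40 AFib cases, 400 enrolled (so 400 − 40 = 360 without AFib), and 10% drop-out. From the Discussion: 5% to 10% compliance problems or losses. Assumed here: the 90% applies at full wear; *m* is the share of watch data missing; values of *m* above 10% are illustrative.

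**The plan's own precision figures.** These are the point estimate minus the lower exact (Clopper-Pearson) 95% bound.

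- Sensitivity, 40 cases: 39/40 gives 97.5 − 86.8 = 10.7 points; a non-integer 99% gives 9.7. Stated: about 10%.
- Sensitivity, 36 cases: 35/36 gives 97.2 − 85.5 = 11.7 points. Stated: 12%.
- Specificity, 360 patients: 324/360 gives 90.0 − 86.4 = 3.6 points. Stated: 4%.
- Specificity, 324 patients: 292/324 gives 3.8 points. Stated: 4%.

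All reproduce after rounding.

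**Effect of the FAS rule.** Two simple wear models:

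- All-or-none (a share *m* of patients has no watch data): specificity = *m* + (1 − *m*) × 0.90; sensitivity = (1 − *m*) × 0.99.
- Partial wear (every patient loses a share *m* of time, with a constant false-alarm hazard): specificity = 0.90^(1 − *m*).

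| *m* | FAS specificity, all-or-none | FAS specificity, partial wear | FAS sensitivity, all-or-none |
|---|---|---|---|
| 0 | 90.0% | 90.0% | 99.0% |
| 5% | 90.5% | 90.5% | 94.1% |
| 10% | 91.0% | 91.0% | 89.1% |
| 30% | 93.0% | 92.9% | 69.3% |
| 50% | 95.0% | 94.9% | 49.5% |

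At *m* = 10% under the all-or-none model, the rule classifies 0.10 × 360 = 36 recorder-negative patients as correct without watch data, and 0.10 × 40 = 4 AFib patients as missed.

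**Early stopping.** If 30% of patients stop after month 1 of 6 (assumed), specificity reads 0.7 × 0.90 + 0.3 × 0.90^(1/6) = 92.5%.

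**Whether the other planned analyses remove it.** The PP set cuts unworn time but keeps the patient. Someone with one worn day and no alarm is still one full true negative, with the same weight as someone who wore the watch for six months. The analysis by analysable time does address non-wear, but it is secondary and measured in time, so it does not correct a per-patient proportion.

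**What the proposed reporting would show.** Take *m* = 10%, all-or-none. The FAS value is 91.0%. Among the 360 − 36 = 324 patients with watch data it is 90.0%. If the other 36 are counted as not correctly classified, it is 0.90 × 324/360 = 81.0%.

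**The case against.** The case for leaving the rule alone has real substance.

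- **The rule is not favourable overall.** A reader might infer that every unworn watch becomes a correct negative and that non-use is reported as better accuracy. The documents do not support that for the FAS. In AFib patients the same rule creates false negatives, and under the all-or-none model 10% missing costs about 10 points of sensitivity against a gain of 1 point in specificity. Sensitivity is also the measure that sizes the trial. This stands.
- **The size is small at the protocol's own rate.** At 5% to 10% the shift is 0.5 to 1.0 point, below the stated 4% precision. This stands, with one reservation: that rate describes compliance problems or losses and is not a ceiling on missing watch time. Table 1 plans to collect daily and nightly hours of use, so partial wear is foreseen.
- **A watch never worn may not enter the analysis.** Section 2.1 defines the intervention as wearing the watch, and patients without intervention or data are excluded. The 100% specificity of a watch left unused may therefore never arise. The text does not say whether the missing data meant are watch data. Early stopping and partial wear remain in any case.
- **The primary specificity is not tied to the FAS.** Both sets are planned and neither is primary, so one cannot say that the primary result is the imputed one. This stands, but per patient the PP set keeps part of the same effect.
- **FAS specificity has a coherent meaning.** An unworn watch raises no false alarm, so the value describes the strategy as offered. That is fair, provided it is labelled so and not read as discrimination.
- **Wear thresholds commonly belong in an SAP.** Their absence is not the finding. The finding is the stated rule, which acts in opposite directions on the two measures.

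A reader might also infer that the PP set turns patients whose AFib occurred only off-watch into AFib-free patients. The article does not spell out how per-patient truth is formed in that set, so this is a possibility and not an established error.

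**Conclusion.** The concern holds for FAS specificity. Scoring missing watch values as no AFib is conservative for sensitivity and anti-conservative for specificity, and the article does not acknowledge the second effect.

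The upward shift is about 0.5 to 1.0 point at 5% to 10% missing, about 3 points at 30% and about 5 points at 50%. The larger figures approach or exceed the stated 4% precision, and unlike sampling error they do not shrink with more patients. They rest on assumed wear rates, most relevant to the impaired-usability subgroups. All figures assume that the planned 90% applies at full wear, which section 2.4 does not say, and that false alarms accrue with worn time or that non-wear is all-or-none. The sensitivity losses shown use the all-or-none model; partial wear could cost less, since later episodes may still be caught.

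The documents do not support a claim that the plan as a whole errs in the watch's favour.

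**What to change.** Keep the rule that missing means no AFib for FAS sensitivity. For specificity, report beside the FAS value:

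1. Per-patient specificity among recorder-negative patients who meet a minimum share of analysable watch time, fixed before results are read and applied whatever the watch showed.
2. A 3×2 table with a separate row for no adequate watch result, and a lower bound that counts the recorder-negative patients in that row as not correctly classified.

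State which analysis set is primary, and label PP accuracy as conditional on worn time. Do not replace the PP truth with the full six-month recorder diagnosis, because the PP analysis would then largely repeat the FAS.

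The cost is analysis wording, since wear is already to be recorded. Reported specificity will be somewhat lower and fewer patients will be evaluable: with 10% not evaluable, 324 instead of 360 gives a precision of 3.8 points instead of 3.6, still within the stated 4%. A patient just above the threshold still has less than full exposure, so some upward drift remains; it is smaller the higher the threshold is set.
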